### Study overview

Overview of the study from inclusion to week 52 is shown in Table 1.

**Table 1 Tab1:** Overview of the study from inclusion to week 52

		Day 0^a^	Day 2	Day 4	Week 1	Week 2	Week 4	Week 8	Week 12	Week 26	Week 52
Treatment	A	No treatment									
	B	Oral prednisolone tapered over 8 weeks									
Medical history		+									
Biochemistry A		+	+	+	+	+	+	+	+	+	+
Biochemistry B		+							+	+	+
Biochemistry C		+			+		+		+		+
Study medication (group B)		+			+	+	+	+			
Blood pressure, HR		+	+	+	+	+	+	+	+	+	+
Clinical examination		+			+	+	+	+	+	+	+
24 h urine		+					+		+		+
Spot urine A		+	+	+	+	+	+	+	+	+	+
Spot urine B		+			+		+		+		+
Questionnaire (SF36)		+					+		+		+

Biochemistry A: P-sodium, p-potassium, p-total calcium, p-ionized calcium, p-phosphate, p-creatinine, eGFR, p-urea, p-glucose, WBC, p-c-reactive protein (CRP), b-sedimentation rate, p-PTH

Biochemistry B: Hemoglobin A1C. p-TSH, p-25-Hydroxy-Vitamine D2 + D3

Biochemistry C: TGF-β1, BMP-7

Study medication: Dose and adverse effects

Clinical examination: Body weight and physical examination

24-h urine collection: Urinary volume and urinary sodium, creatinine, and albumin excretion

Spot urine A: Urine-dip stick (hemoglobin, protein, leucocytes, glucose, nitrite), urinary albumin and creatinine concentrations and urinary albumin/creatinine ratio

Spot urine B: Urinary concentration and ratios in relation to urinary creatinine of TGF-β1, BMP-7, A1M, B2M, MCP-1, NGAL, NAG, IL-18, TIMP-2, KIM-1, IGFBP7 and CD163-

Questionnaire: SF36 is filled in by the patient

^a^Before start of study medication

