#### Randomization

Randomization is performed locally and electronically using REDCap (www.redcap.au.dk; Clinical Trial Unit, Aarhus University). Randomization is performed 1:1 in blocks of 6. Since only a few subjects are expected to be included each center, any center effects are considered insignificant. Neither clinicians nor patients are blinded to the study treatment group.

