### Study treatment

Subject are randomized to one of two treatments:
Group A (controls): No trial medicationGroup B: Oral prednisolone for 8 weeks with dose tapering (Table 2)

**Table 2 Tab2:** Prednisolone dosages and tapering over 8 weeks after inclusion

Prednisolone dosing regime		
Day	Week	Dose (mg/day)
1–14	1–2	60
15–28	3–4	40
29–35	5	30
36–42	6	20
43–49	7	10
50–56	8	5

Deviations from the dose-tapering regimen are tolerated if considered of vital clinical importance as per discretion of the local investigator. Such deviations are recorded in the electronic case report form (eCRF).

Monitoring of compliance with prednisolone is performed at study visits by interview, as well as by counting the returned study medication after cession of intake.

Prednisolone is used extensively in nephrology patients, and most nephrologists are familiar with the drug. Prednisolone is administered to the patients with-out costs. Side effects are expected in most cases. Adverse reactions will be registered in eCRFs at all planned clinical visits and from the questionnaires.

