##### Additional exploratory analysis

The exploratory analyses include analysis of biomarkers in urine and plasma and the evaluation of these biomarkers in relation to renal prognosis. Renal biopsies form the included patients will be systematically re-evaluated to identify possible renal prognostic factors. The re-evaluation will include the presence and quantification of eosinophilic granulocytes, degrees of inflammation and fibrosis and additional staining for special biomarkers such as TGF-β1 and BMP-7. Safety end-point such as development of diabetes mellitus, infection rate, hospital admission and death will be explored.

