## Methods

The local investigators are responsible for patient recruitment, clinical follow up, data entry in Redcap and shipment of centrally analyzed biochemical samples (biomarkers).

Blood and urine from biochemistry A, biochemistry B, 24-h urine collection and spot urine A, are analyzed at the local clinical biochemistry laboratory using standardized automated procedures. The CKD-EPI formula is used to calculate eGFR [47]. Similar, standardized and national reference intervals are applied by all clinical biochemistry laboratories in Denmark.

Blood sample C and spot urine B are analyzed at The University Clinic of Nephrology and Hypertension, Gødstrup Hospital using commercially available assays based on ELISA or RIA methods. Samples are centrifuged and frozen locally at − 80 °C, shipped to the central lab and stored in a research biobank at − 80 °C, until analyzed. Supplementary analyses of the material not described in the protocol is subject to additional approval by the scientific ethics committee.

Quality of life is estimated with the SF-36 questionary which the patients fill in 4 times during the study period [48, 49].

Safety estimates are evaluated in several ways. This includes the frequency of side effects, adverse events and hospital admissions, which are reported continuously by treating physicians in the eCRF. Development of diabetes in estimated by momentary and long term blood glucose levels (Hemoglobin A1c) and new onset hypertension from the blood pressure levels and medical chart reported in eCRF.

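### Table 1 schedules adverse-effect recording only for the prednisolone arm and only to week 8, which conflicts with the text; visit-based recording in the control arm is nowhere explicit

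*Protocol article*

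**What the plan says.** All references are to the protocol article.

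- **Study overview, Table 1.** The only row that covers adverse effects is the one whose label begins "Study medication (group B". The notes define its content as "Study medication: Dose and adverse effects". It is marked at day 0 (before the drug is started) and at weeks 1, 2, 4 and 8.
- **Study treatment.** "Adverse reactions will be registered in eCRFs at all planned clinical visits and from the questionnaires". The sentence closes a paragraph about prednisolone.
- **Methods, on safety.** "This includes the frequency of side effects, adverse events and hospital admissions, which are reported continuously by treating physicians in the eCRF". No arm or time limit is given. The section continues: "Development of diabetes in estimated by momentary and long term blood glucose levels (Hemoglobin A1c) and new onset hypertension from the blood pressure levels".
- **Additional exploratory analysis.** "Safety end-point such as development of diabetes mellitus, infection rate, hospital admission and death will be explored".
- **Randomization.** "Neither clinicians nor patients are blinded to the study treatment group".

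**The concern.** The three places do not describe the same procedure. Table 1 ties adverse effects to the drug row of one arm and stops at the end of the taper. Study treatment covers every planned visit. Methods relies on ongoing physician reports. A site could reasonably build its visit routine from Table 1. It would then ask group B about adverse effects at set visits and leave group A to whatever the physician happens to report.

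This matters because the Discussion justifies the trial by setting possible renal benefit against the harms of steroids. Infections and subjective side effects are found more often when patients are asked. Both patients and physicians know the allocation, and the Discussion already accepts that this may bias reporting. Prompting only one arm would add to that bias and make prednisolone look more harmful than it is.

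**Working it through.** The plan states no figure on this point, so the check is a comparison of passages, followed by a simple sensitivity calculation.

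**1. Marks in Table 1** (10 columns: day 0, day 2, day 4, weeks 1, 2, 4, 8, 12, 26, 52)

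| Item | Arm label | Columns marked | Marked after week 8 |
|---|---|---|---|
| Dose and adverse effects | group B | 5 of 10 | none |
| Adverse effects, group A | no such row | 0 of 10 | none |
| Clinical examination | none | 8 of 10 | weeks 12, 26, 52 |
| Blood pressure | none | 10 of 10 | weeks 12, 26, 52 |
| Biochemistry A (includes glucose) | none | 10 of 10 | weeks 12, 26, 52 |
| Biochemistry B (includes HbA1c) | none | 4 of 10 | weeks 12, 26, 52 |

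The adverse-effects row spans 8 of 52 weeks. It leaves 52 − 8 = 44 weeks unmarked, and 44/52 = 85%.

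**2. Table 1 against Study treatment.** If every planned visit is a recording point, weeks 12, 26 and 52 should carry a mark. Days 2 and 4 should too, if those contacts count as clinical visits. Table 1 marks none of them, so the two statements cannot both govern the eCRF.

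**3. Does Study treatment cover group A?** Not explicitly. It speaks of adverse reactions, directly after text on the use and expected side effects of prednisolone, and an untreated control has no reaction to a drug not given. The only questionnaire in Table 1 is the SF-36, which Methods describes as a quality-of-life measure.

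**4. Does Methods cover group A?** Yes for reporting in general: it has no restriction by arm or week. It sets no prompt at visits. Read together with Table 1, group B has scheduled recording plus physician reports, and group A has physician reports only.

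**5. Which endpoints are exposed?**
- *Diabetes and new hypertension:* assessed from glucose, HbA1c, blood pressure and the chart. The measurements sit in rows with no arm label and run to week 52. Largely protected.
- *Death:* does not depend on asking. Largely protected.
- *Hospital admission:* named in the continuous reporting, and a hard event. Little exposed.
- *Infection and subjective side effects:* depend on being asked about or volunteered. Exposed.

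**6. Possible size.** Let p be the true rate, the same in both arms, and c_A and c_B the proportions of events captured. The observed relative risk is (p × c_B)/(p × c_A) = c_B/c_A, whatever p is. The documents give none of these values. The figures below are assumptions, with p = 20% and 55 patients per arm as planned.

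| c_B | c_A | Observed B | Observed A | Relative risk | Difference in patients |
|---|---|---|---|---|---|
| 90% | 90% | 0.20 × 0.90 = 18% | 18% | 1.0 | 0 |
| 90% | 80% | 18% | 0.20 × 0.80 = 16% | 18/16 = 1.13 | 0.02 × 55 = 1.1 |
| 90% | 60% | 18% | 0.20 × 0.60 = 12% | 18/12 = 1.5 | 0.06 × 55 = 3.3 |

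**The case against.** The strongest reply is that Methods is the general rule for safety and already covers both arms for the whole follow-up. On this view the Table 1 row is drug accountability, with side effects noted while tablets are dispensed. The table is called an overview, and the layout of the adverse-event form belongs to the full protocol and the eCRF, which are not shown. Nothing says that controls are not asked. The endpoints concerned are exploratory.

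Much of this stands, and it rules out two stronger readings that a reader might take from Table 1:

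- *That nothing is checked after the taper.* Study treatment, read alone, includes the later visits. Examination, blood pressure, glucose and HbA1c are scheduled at weeks 12, 26 and 52 without restriction by arm. Every HbA1c after day 0 falls after week 8.
- *That the plan lays down unequal ascertainment.* It does not. Continuous reporting applies to both arms, and capture may in practice be equal. The relative risk of 1.5 only restates an assumed 90% against 60%. It is not evidence of bias in this trial.

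The reply does not remove the conflict between the table and the text. That is a difference between two printed rules, not detail left out for brevity. Nor does it supply a statement that group A is asked at its visits.

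**Conclusion.** The point holds as an inconsistency that carries a risk of bias. Table 1 limits scheduled adverse-effect recording to group B and to week 8. Study treatment and Methods are wider, and none of the three makes visit-based recording in group A explicit. If Table 1 is followed as printed, infections and subjective side effects may be captured unequally, most likely to the disadvantage of prednisolone.

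The size cannot be derived from the documents. Over the assumed range the spurious relative risk runs from 1.0 to 1.5, or from 0 to about 3 extra patients with a recorded event in group B. This rests on equal true rates, on sites following the table rather than the text, and on prompting raising capture. Diabetes, hypertension and death are largely protected. The primary outcome and the sample size are not affected. The correction is worth making, because events not asked about at past visits cannot be fully recovered at analysis.

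**What to change.** Reconcile Table 1 with Study treatment and Methods:

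1. Give adverse events their own row in Table 1 with no arm label, marked at every clinical visit to week 52. State whether the day 2 and day 4 contacts count.
2. Use one eCRF form with the same questions in both arms, covering at least infection, new diabetes, hypertension and hospital admission. Keep continuous physician reporting alongside it.
3. Keep dose and compliance as the group B row.
4. In Study treatment, refer to adverse events in both arms, and say which questionnaire, if any, collects them, since the SF-36 measures quality of life.
5. The article reports 30 patients already included. If the eCRF followed Table 1 for them, record the date from which the common form applied, so that the safety tables can be read accordingly.

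The cost is one form and a few minutes at visits that already take place. No extra visits or samples are needed.

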### Study treatment

Subject are randomized to one of two treatments:
Group A (controls): No trial medicationGroup B: Oral prednisolone for 8 weeks with dose tapering (Table 2)

**Table 2 Tab2:** Prednisolone dosages and tapering over 8 weeks after inclusion

Prednisolone dosing regime		
Day	Week	Dose (mg/day)
1–14	1–2	60
15–28	3–4	40
29–35	5	30
36–42	6	20
43–49	7	10
50–56	8	5

Deviations from the dose-tapering regimen are tolerated if considered of vital clinical importance as per discretion of the local investigator. Such deviations are recorded in the electronic case report form (eCRF).

Monitoring of compliance with prednisolone is performed at study visits by interview, as well as by counting the returned study medication after cession of intake.

Prednisolone is used extensively in nephrology patients, and most nephrologists are familiar with the drug. Prednisolone is administered to the patients with-out costs. Side effects are expected in most cases. Adverse reactions will be registered in eCRFs at all planned clinical visits and from the questionnaires.

#### Other treatment

Patients allocated to prednisolone are advised to take oral vitamin D3, 20 μg daily. Furthermore, a proton pump inhibitor is recommended while the dose of prednisolone exceeds 15 mg/day, unless this is considered the precipitating cause of AIN. Bisphofonates are not recommended; however, patients already taken these at inclusion will continue.

No other immunosuppressive treatment may be prescribed during the study; however, other additional treatment is allowed as per local guidelines and at the discretion of the local investigator. Hypertension should be treated aiming at a blood pressure < 140/90 mmHg. Fluid retention should be treated with diuretics, sodium- and fluid restriction or dialysis as required [45]. Diabetes mellitus is diagnosed and treated according to standard guidelines and at the discretion of the local investigator [46]. Dialysis is initiated and performed based on the discretion of the local investigator [45].

### Endpoints

#### Primary

eGFR 3 months after inclusion (eGFR for patients on dialysis at 3 months is defined as “0 ml/min/1.73 m^2^).

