#### Secondary

Renal function and changes in this defined by:
Plasma creatinine (3 and 12 months)eGFR (12 months)Change in plasma creatinine at 3 and 12 months from the following time-points
○ Highest measured plasma creatinine during the cause of AIN○ Plasma creatinine at time of renal biopsy○ Plasma creatinine at day 0 (inclusion)Number of patients with end stage renal failure and RRT (chronic dialysis or transplantation)For patients in whom a prior, baseline p-creatinine is available, the following will be analyzed
○ Number of patients not on renal replacement therapy who returns to baseline creatinine or lower within 3 and 12 months after inclusion.○ Difference between p-creatinine after 3 and 12 months and baseline.Baseline p-creatinine is defined as the last recorded p-creatinine while the patient’s condition is considered as stable. If more than one such measurement is recorded within the last year, the baseline value is calculated as the average of the last 3 measurements. If more than one measurement is present from the same day an average of these measurements will be included as one of the 3 last measurements.In the prednisolone treated group the importance of “treatment delay” is analyzed by examining eGFR at 3 and 12 months. This will be explored using three different definitions of treatment delay:
○ Days from first symptom to inclusion in this project and initiation of prednisolone○ Days from first contact to the Danish health care system to inclusion in this project○ Days from first contact to a nephrology department to inclusion in this projectQuality of life estimated by a questionnaire (SF 36) at and 12 months

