### Statistics

The primary analysis will be performed as “intention to treat”, and the secondary analysis as “treated as”. Normally distributed variables are compared by unpaired t-test or one-way ANOVA. Repeated measures are analyzed using a general linear model (GLM). Comparable non-parametric tests are used in case of non-normally distributed variables. Both absolute and relative proportions are analyzed. Secondary end-points are analyzed as differences in absolute or relative proportions. Analysis of factors affecting the primary end-point will be performed using a GLM. Kaplan Meier curves will be used when appropriate e.g. in the evaluation of time to end stage renal failure. Any correlation between the primary end point and relevant secondary outcomes and outcomes form the exploratory analysis will be evaluated with appropriate adjustment for potential confounders.

Sample size was estimated for the primary outcome based on a clinical relevant 10 ml/min/1.73m^2^ difference in renal function (eGFR, CKD-EPI) between groups at 3 months, a standard deviation of 18 ml/min, a power of 0.80 and a significance level of 0.05. This showed that 51 patients should be included in each group. Anticipating dropouts, we estimate that 55 patients in each group are necessary and plan to randomize 110 patients.

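### The withdrawal rule, read with the exclusion list, removes patients for poor renal outcome (CKD stage IV-V) or prednisolone intolerance, although the endpoints and the intention-to-treat analysis need those patients to stay under observation

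*Protocol article*

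**What the plan says.** All references are to the protocol article.

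- **Withdrawal criteria** gives two reasons for withdrawal: coming to meet any of the exclusion criteria, and withdrawing consent.
- **Exclusion criteria** lists CKD stage IV-V and prednisolone intolerance among others. Neither is tied to a time before inclusion. The immunosuppression criterion, by contrast, is anchored to the months before biopsy.
- **Endpoints, Primary** is eGFR at 3 months, and "eGFR for patients on dialysis at 3 months is defined as" zero.
- **Endpoints, Secondary** includes eGFR at 12 months and the "Number of patients with end stage renal failure and RRT (chronic dialysis or transplantation").
- **Statistics** makes the primary analysis intention to treat and adds that "Kaplan Meier curves will be used when appropriate e.g. in the evaluation of time to end stage renal failure". On sample size it says: "Anticipating dropouts, we estimate that 55 patients in each group are necessary and plan to randomize 110 patients".
- **Table 1** schedules creatinine and eGFR at every visit up to week 52, including weeks 12, 26 and 52.

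**The concern.** Severe loss of renal function is the bad end of the scale on which this trial is judged. A rule that withdraws patients when they reach it makes missing data depend on the outcome. If prednisolone works as hypothesised, more controls reach stage IV-V and more controls leave. The controls who remain then look better than the group that was randomised, and the difference shrinks towards zero. The count of end stage renal failure and the curve of time to it can lose the patients who were about to contribute events.

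Intolerance works differently. It arises essentially only in patients given prednisolone, so those withdrawals fall almost wholly in one arm. Neither kind of loss is ignorable. An intention-to-treat label does not repair it, because that analysis cannot use measurements that were never taken.

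**Working it through.** **1. The plan's own sample size.** The inputs are a difference of 10 ml/min/1.73m² and "a standard deviation of 18 ml/min, a power of 0.80 and a significance level of 0.05" (Statistics). Taking the test as two-sided:

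n per arm = 2 × (1.960 + 0.842)² × 18² / 10² = 2 × 7.85 × 324 / 100 ≈ 50.9, so 51.

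This reproduces the stated 51. By the same normal approximation, power is 0.80 at 51 per arm and 0.83 at 55. The dropout allowance is (55 − 51) / 55 = 7.3%, or 8 patients of 110. The calculation itself is sound.

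**2. The rule against each result that needs the patient.**

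| Result | What it needs | What the rule does as written |
|---|---|---|
| 3-month eGFR, dialysis scored 0 | Dialysis patients still in the study at week 12 | Withdraws anyone labelled CKD IV-V or intolerant before then |
| 12-month eGFR | Poor recoverers still in the study at week 52 | Withdraws those who reach CKD IV-V at any time in the year |
| Count of end stage renal failure and RRT | Follow-up through stage IV-V | Withdraws at or before the event |
| Time to end stage renal failure | The same | If withdrawal ends follow-up, the patient can only be censored, and for a reason tied to the event |
| Intention to treat | Outcomes on all randomised patients | Ends observation for some of them |

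**3. What withdrawal can mean.** Group A receives no trial medication (Study treatment). For that arm withdrawal cannot mean stopping study drug; it can only mean leaving the study.

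**4. Size for end stage renal failure.** Background gives a 5–7% risk of dialysis-requiring end stage disease after biopsy-proven AIN. If that applied here, 110 × 0.05 = 5.5 and 110 × 0.07 = 7.7, so about 6 to 8 patients in the whole trial. With so few events, losing two or three changes the result.

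**5. Size for the 3-month endpoint.** A patient found to have a low eGFR at the week 12 visit already has the primary outcome recorded, so later withdrawal cannot remove it. Only withdrawals before that visit matter, and the article gives nothing from which to count them. An extreme case can still be drawn. Suppose everyone whose 3-month eGFR would fall below 30 had been withdrawn beforehand. The cut-off of 30 and the control means are assumptions; SD 18, a true difference of 10 and 55 per arm are the plan's figures.

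The mean of those remaining is μ + σ·φ(a)/(1 − Φ(a)), with a = (30 − μ)/σ. For a control mean of 40:

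- Controls: a = −0.556, so 40 + 18 × 0.342/0.711 = 48.7.
- Prednisolone, mean 50: a = −1.111, so 50 + 18 × 0.215/0.867 = 54.5.
- Remaining difference: 5.8 instead of 10.

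Simulation with 20,000 runs per row, t-test:

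| Control mean | Removed, control vs prednisolone | Difference | Power |
|---|---|---|---|
| 30 | 50% vs 29% | 4.4 | 0.30 |
| 40 | 29% vs 13% | 5.8 | 0.49 |
| 50 | 13% vs 5% | 7.4 | 0.66 |
| 60 | 5% vs 1% | 8.7 | 0.75 |

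With nobody removed, power is about 0.82. With a cut-off of 15, power runs from 0.58 (control mean 30) to 0.81 (control mean 60). These rows show the direction and an upper limit for CKD-driven loss under each assumption. They do not estimate what will happen to the primary analysis.

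**The case against.** **The authors probably meant pre-existing CKD.** Patients enter with raised or rising creatinine, and Background says that dialysis is needed in 40% of the acute cases it describes. If a low eGFR alone met the criterion, many target patients would be excluded on day 0. This stands as an account of intent, and it is why a low eGFR during the acute illness cannot simply be equated with CKD IV-V. It does not rescue the text: the withdrawal rule is about criteria that arise after inclusion, and the CKD criterion carries no limit to earlier disease. Background treats CKD as a consequence of AIN, and the Discussion weighs small 3-month differences in late stage CKD, so such patients are expected in the comparison.

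**Intention to treat and the zero score for dialysis show that retention was intended.** They do point that way, which is why the passages conflict. The intention does not secure the measurements.

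**A journal article need not describe follow-up after withdrawal.** That is correct, and its silence is not the point here. The point is a printed rule that clashes with printed endpoints.

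**Intolerance is partly covered.** Study treatment allows and records taper deviations, and an as-treated analysis is planned alongside intention to treat. This softens the intolerance part but leaves the withdrawal rule in place.

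A reader might go further and infer that the 0.80 power no longer holds for the primary endpoint, or quote 0.49 to 0.75 as the real power. The document does not support this. Those figures remove patients by their own week 12 value, treat every eGFR below 30 as CKD IV-V, and rest on assumed control means. Nor does the article say that withdrawal deletes data already collected or that the Kaplan-Meier analysis censors at withdrawal.

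**Conclusion.** The point holds as a contradiction within the article. It follows from the text alone: the withdrawal and exclusion sections, taken together, remove patients whom the primary and secondary endpoints and the intention-to-treat analysis need.

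The 12-month eGFR and the end stage renal failure count and curve are most exposed, because a full year is available for patients to reach CKD IV-V. About 6 to 8 end stage cases are expected if the cited 5–7% applies. The 3-month primary endpoint is exposed only through patients labelled CKD IV-V or intolerant, and withdrawn, before week 12. How many that would be cannot be computed from the document.

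If the arms differ in renal outcome, CKD-driven loss is greater in the worse arm and biases towards no difference. The direction of any bias from intolerance withdrawals is not determined by the document. The conclusion assumes that withdrawal means leaving follow-up, which is the only meaning available for group A.

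**What to change.** Reconcile the Withdrawal criteria and Exclusion criteria sections with the endpoints and Statistics:

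- State that an exclusion criterion arising after randomisation does not end follow-up or remove data, and that only withdrawal of consent ends data collection.
- State that CKD stage IV-V, dialysis and prednisolone intolerance arising after randomisation are recorded as outcomes.
- Keep the week 12, 26 and 52 assessments for all randomised patients, at minimum creatinine and dialysis status, and keep all of them in the intention-to-treat analysis.
- For anyone already withdrawn under the rule, retrieve 3- and 12-month creatinine and dialysis status where consent allows.

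Whether study drug continues in such a patient is a separate matter for the investigators and is not addressed here.

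The cost is a wording amendment and routine laboratory and dialysis data on a few patients, with no increase in sample size. It should be made while patients are still in follow-up, because 12-month measurements that are not taken may not be recoverable.
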